### Study Program

#### Overview

Participants will be involved in the trial for approximately 2 months, including a 3-week intervention period in which they will be randomized to 1 of the 3 training arms, followed by a 1-month follow-up period. Several strategies will be used to maximize participant retention and follow-up completion. First, we will adopt a web-based completion mode for the surveys and training sessions. Second, participants will receive a personalized email invitation for each training session. These emails will also provide participants the opportunity to ask the research team about any technical difficulties or other obstacles encountered while using the software. Third, we will use a combination of SMS text message and email message reminders according to the participants’ preferences. These reminders will be sent to the participants who do not complete the scheduled session within 24 hours of receiving the weblink. When there is no reaction to the training sessions and reminders after 2 weeks (ie, after 4 training sessions and 4 reminders), the participant will be considered as a dropout. Similarly, participants who fail to complete the follow-up assessments will receive up to 2 emails or SMS text message reminders: one after 24 hours and another one after 48 hours. Finally, the gamified ABMT intervention was developed using gamification features to encourage participants to keep using the program. No incentives will be provided to the participants.

Participant care (eg, rehabilitation program, exercise, cognitive behavioral therapy, and pain medications) concomitant with the ABMT (ie, control ABMT, standard ABMT, or gamified ABMT) will be permitted during the trial. It will be monitored through a *pain-treatment* question that will probe participants’ pain treatments and frequency since the commencement of the study or previous assessment.

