### Procedure

After informed consent is obtained and participants are eligible, they will complete the web-based baseline assessment (approximately 35 minutes) containing demographic questions as well as questions relating to their general health, current mental health, pain experience, and everyday thoughts and behaviors. At the end of the survey, participants will select their preferred days for training, which will be either (1) Monday and Thursday or (2) Tuesday and Friday. Participants will also be asked to provide an email address so that the research team can send links to the training sessions. Participants will then be randomized into 1 of the 3 groups and be invited by email to start their first training session. This email will include a weblink to the appropriate version of the intervention, as well as instructions on how to download the program.

Training sessions will be performed on the web at the participants’ time and place of convenience (using their own computers), twice a week on a separate pair of days (Monday and Thursday or Tuesday and Friday) for 3 consecutive weeks, totaling 6 sessions. This dosage is based on previous pain ABMT literature, which has shown positive training effects for dosages ranging between 4 and 8 sessions [4,7,8]. It is anticipated that the first and final sessions will take approximately 30 minutes, as it includes cognitive assessment measures, whereas sessions 2 to 5 will take approximately 15 minutes to complete. Participants will be asked to complete the sessions during normal waking hours and within 24 hours of receiving a web link. Each session will start with the same instructions, similar to those of previous research [10], and highlight the need to create a quiet and private environment free from distractions for at least 30 minutes. In total, the participants will be sent 6 session links. Necessary reminders will be sent via email and SMS text messages throughout the study.

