### Sample Size Estimation

To the best of our knowledge, there are no similar published studies on gamified pain ABMT or ABMT for adults with chronic pain that directly compare 3 groups (ie, control ABMT, standard ABMT, and gamified ABMT); therefore, there is no previous effect size on which to base a sample size estimation. As such, a minimum sample size of 30 per training group is planned on the basis that this exceeds the sample size determined by several similar pain ABMT and gamified training studies [7,10,80]. Sharpe et al [7] determined that a sample size of 12 per group was enough to achieve 82% power with a significance level of .05 for their study of ABMT in adults with chronic pain that compared 2 groups (ABMT vs placebo), for which a medium effect size (Cohen *d*=0.45) on pain interference was found in the intervention group (ABMT: n=22; placebo: n=12). Heathcote et al [10] determined a sample size of 20 per group for their study of ABMT in adolescents with chronic pain that compared 3 groups (ie, ABMT, placebo, and waitlist). Boendermaker et al [80] observed in their study, which involved a sample size of <20 per group, that gamified cognitive bias modification training (for alcohol problems) had a positive impact on motivation to train compared with regular training. Considering attrition rates of previous trials in chronic pain treatment [81] and given the 1-month follow-up measurement, a dropout rate of approximately 30% is expected for the current trial. Therefore, a total target sample size of 120 participants (40 participants per group) will be sought. To help achieve adequate participant enrollment, we developed engaging recruitment materials and selected multiple channels for delivery.

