### Statistical Methods

#### Overview

Statistical analyses will be conducted after data collection is completed using the SPSS version 27.0 or later (IBM Corp). Continuous data will be presented as means and SDs, whereas categorical data will be presented as frequencies and percentages. Analyses will follow the intention-to-treat principle and will include all randomized participants who successfully complete at least one training session (ie, minimum threshold exposure to ABMT). To determine whether there are any pretraining differences between the training conditions on demographic variables and baseline characteristics, a series of analyses will be performed. The rates of and reasons for missing data will be reported. To manage missing data, the study will attempt to follow-up on all randomized participants (even if they withdraw from the trial) and, where appropriate, use multilevel modeling for repeated measure data analyses as it allows the incorporation of all available data. Significance for all statistical tests will be set at *P*<.05 (2-tailed). Effect sizes will be presented by its most appropriate effect size (and 95% CI), as described by Lakens [82], with a preference for Cohen *d* where possible [83]. No interim analyses of the trial outcome data are planned.

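### Two reminders ending at 48 hours are a thin procedure for the 1-month primary pain outcomes; later automated reminders would be a cheap improvement

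*Protocol article*

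**What the plan says.** Under Study Program, Overview, the protocol article sets the rule for "participants who fail to complete the follow-up assessments": they "will receive up to 2 emails or SMS text message reminders: one after 24 hours and another one after 48 hours". The same section offers no incentives. It classes someone as a training dropout after two weeks without reaction, that is "after 4 training sessions and 4 reminders".

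The Procedure section adds a general line: "Necessary reminders will be sent via email and SMS text messages throughout the study". It gives no number or timing. It also says that the 1-month invitation goes to all participants, whereas the posttraining invitation follows completion of the last training session.

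Table 1 places both primary pain measures (PROMIS Pain Intensity 3a and Pain Interference 8a) at baseline, posttraining and 1 month.

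Sample Size Estimation states that "a dropout rate of approximately 30% is expected for the current trial". Statistical Methods, Overview, states that "the study will attempt to follow-up on all randomized participants (even if they withdraw from the trial"), and relies on multilevel models for the repeated measures.

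**The concern.** The trial runs entirely on the web, with no visits and no incentives. Once the 1-month invitation has gone out, the two reminders are the main active means of getting an answer. Someone who is away or unwell for a few days passes both and, on the stated schedule, hears nothing more. That is little effort for a primary outcome when nearly a third of participants may be lost and the stated aim is to try to follow up all of them.

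Two things are at stake. One is precision at 1 month, where the expected number of respondents already falls below the plan's own minimum. The other is the credibility of the between-group pain comparison. A multilevel model uses whatever was observed, but it does not remove bias if non-response depends on the unobserved pain score. Obtaining the data is the better protection.

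**Working it through.** Inputs:

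- Target: "a total target sample size of 120 participants (40 participants per group) will be sought" (Sample Size Estimation).
- Minimum: "a minimum sample size of 30 per training group is planned" (same section).
- Loss: about 30% (same section).
- Significance level: 5%, two-sided (Statistical Methods, Overview).
- Standardized effect of 0.45 on pain interference, cited from an earlier two-group study (Sample Size Estimation). It is not this trial's design effect and serves only as an illustration.
- Share of participants recovered by later reminders: not in the document. Assumed here to be 5 to 10 percentage points.

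**Step 1: the plan's own figure.** Inflating 30 for 30% loss gives 30 / (1 − 0.30) = 42.9, so 43 per group and 129 in total, not 40 and 120. Multiplying instead gives 30 × 1.30 = 39 per group, 117 in total, which is close to the stated target. The target is exact at 25% loss: 30 / 0.75 = 40. The loss is stated only as approximate, and the inflation is a separate sample-size matter. Here it shows only that the target has no slack.

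**Step 2: respondents at the stated loss.** 40 × 0.70 = 28 per group, 84 in total, with 12 lost per group.

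**Step 3: respondents under the assumed recovery.**

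- 5 points: 40 × 0.75 = 30 per group, which is 2 of the 12 losses (one in six).
- 10 points: 40 × 0.80 = 32 per group, which is 4 of the 12 (one in three).

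**Step 4: standard errors.** With the standard error proportional to 1/√n:

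- √(28/30) = 0.966, or 3.4% smaller.
- √(28/32) = 0.935, or 6.5% smaller.

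These are upper figures. They treat a non-respondent as contributing nothing, whereas in the planned model a person missing only the 1-month survey still contributes baseline and posttraining scores. They also assume that those recovered had completed at least one training session, since the analysis set requires it.

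**Step 5: illustration in power.** For one pairwise comparison at d = 0.45, power = Φ(d√(n/2) − 1.96):

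- n = 28: 0.45 × 3.742 − 1.96 = −0.276, power 39.1%.
- n = 30: 0.45 × 3.873 − 1.96 = −0.217, power 41.4%.
- n = 32: 0.45 × 4 − 1.96 = −0.16, power about 44%.

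Even if half of all losses were recovered (34 per group), power would be 45.8%, against 52.1% with no loss. The gain is real but modest.

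**The case against.** Several stronger readings are tempting, and the document does not support them.

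- **That the rule breaks a promise.** The text commits only to an attempt. Inviting everyone and reminding every non-respondent twice is an attempt. This objection stands.
- **That the survey is chased less hard than the training.** Four reminders for four missed sessions is one per session, and the two weeks are simply the time that four sessions span. Per task, the survey gets more reminders. This stands, so the contrast with training carries no weight.
- **That answers are lost after 48 hours.** Nothing says that the link closes or that late answers are refused. What stops, on the stated schedule, is the prompting.
- **That all 12 expected losses per group could be recovered.** The 30% is not split between people who stop training and people who do not answer a survey, and some will have withdrawn for good.
- **That the hypothesized difference in dropout between arms shows bias in the pain comparison.** Aims and Hypotheses pairs dropout with sessions completed, and the attrition measure concerns stopping the intervention. It makes differential survey response plausible but does not establish it.
- **That the same extension belongs on the posttraining survey.** It is unclear whether the reminder rule covers that survey. Its invitation follows the final session, so someone who stopped training may never receive one. With 7-day recall, an answer on day 14 would no longer describe pain immediately after training.

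The general line on necessary reminders is a fair point for the authors, but it sets no schedule and does not displace the specific limit of two. What remains is that no prompt after 48 hours is described for the 1-month primary outcomes.

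**Conclusion.** The point holds as a cheap improvement to retention at 1 month. It is neither an error nor a contradiction in the plan. At the stated loss, 28 per group would respond against a minimum of 30, and recovering 2 of the 12 losses per group would close that gap. If later reminders brought back 5 to 10 percentage points, 30 to 32 per group would respond, and standard errors at that time point would fall by at most about 3% to 7%.

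The conclusion rests on three assumptions: the yield, for which the document gives no figure; loss being about equal across groups; and at least part of the loss being survey silence rather than final withdrawal. If almost all of it is withdrawal, the gain is close to nil, but so is the cost.

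**What to change.** For the 1-month survey only, sent to all randomized participants including those who stopped training:

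1. Keep the 24- and 48-hour reminders and add automated ones at about day 7 and day 14 after the invitation.
2. Make the last contact a short form with only the 11 primary pain items (3 from PROMIS Pain Intensity 3a and 8 from Pain Interference 8a).
3. Accept answers up to about 14 days after the invitation under the 1-month time point, and record the response date.

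Leave the posttraining window as it is, but state whether the two-reminder rule covers that survey.

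The cost is a change to automated message settings and a minor ethics notification, with no extra enrolment. Participants receive one or two more messages. Some 1-month answers will arrive up to two weeks late, so their 7-day recall period shifts by as much. The recorded dates allow response timing to be compared between groups.

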#### Task Stimuli

Pain words were chosen as stimuli instead of pictures, as meta-analytic results have shown that biases for pain-related information are larger when using (sensory) pain words than when using pictorial stimuli [3]. Furthermore, a study directly comparing ABMT protocols using words versus facial expressions found that attentional biases changed in the predicted direction on the stimuli presented during the training; however, for those trained on words, training effects also generalized to pictorial stimuli [25]. Finally, words have the advantage of being relatively quick to process, easy to implement, and their physical characteristics (eg, word length) can be tightly controlled [26].

A total of 3 sets of word stimuli will be used. The stimulus set for the practice trials (set 1) will comprise 8 neutral word pairs related to the categories of natural (eg, *log*) and manmade (eg, *pot*) resources. The stimulus set for the experimental trials (set 2) will comprise a set of 8 pain-related words and 8 neutral words. The stimulus set used for the assessment of attentional bias trials (set 3) will comprise 8 different pain-related and neutral word pairs, with the same words presented at pre- and posttraining assessments to investigate the generalization of training effects. Pain words stem from 2 different pain-related categories: sensory (eg, *sharp*) and affective (eg, *agonizing*) pain words. To control for the semantic relatedness of the word set, each pain-related word (eg, *pain*) is matched with a neutral (ie, nonpain) word (eg, *bird*) for length and frequency of use in the English language [27]. Word stimuli in each set will be unique, that is, not replicated in any other set. Each word stimulus will be presented in a black 28-point upper-case Courier New font on a white background. All word stimuli will be taken from a data set of stimulus material, previously created and validated for use in chronic pain samples by the authors of this study ([name], [name], [name], [name], [name], unpublished data, April 2020). Specifically, in that study, we reviewed the literature on dot-probe studies investigating attentional biases, selected a pool of pain-related and matched neutral words for validation, and then asked participants with and without chronic pain to complete a speeded word categorization paradigm and rate the pain relatedness of a subset of pain words. For this study, we selected sensory and affective pain words that (1) were rated as most relevant to chronic musculoskeletal pain and (2) were categorized the quickest as pain related by adults with chronic pain.

#### Experimental Tasks

#### Overview

Tasks will be programmed and presented using Inquisit 6.4 (Inquisit Web Millisecond software package) on participants’ internet-connected desktop or laptop computers. Participants will be required to download and install the application using a plug-in. At the end of each training session, a data file containing their RT and accuracy scores will be automatically and securely saved to the researcher’s web-based Inquisit account. To account for different screen sizes and ensure consistency in the display of word stimuli across participants, a calibration process will be completed at the start of each session. Participants will be asked to place a credit card (which is universally the same size) on the screen and adjust the length of a horizontal line until it matches the width of the credit card.

All conditions (standard ABMT, control ABMT, and gamified ABMT) will use a modified version of the dot-probe task [5]. Each task starts with a 500-millisecond duration fixation cross to direct attention to the center of the computer screen (Figure 2). Then, a randomly selected stimulus pair comprising 1 pain-related and 1 neutral word will appear for 500 milliseconds, with 1 word located at the top of the screen and the other at the bottom. The word stimuli will be centered horizontally. Once the pairings disappear, a probe (ie, *p* or *q*) replaces the location of one of the words. Participants will be instructed to determine whether a *p* or a *q* appears and respond as quickly and as accurately as possible by pressing the corresponding keys (ie, *p* key pressed with the right index finger and *q* key pressed with the left index finger) on the computer keyboard. The probe will disappear as soon as a response is recorded or after 2500 milliseconds. The intertrial interval will be 500 milliseconds.

To ensure that participants’ attention is directed toward the center of the screen, several digit trials will be presented [10,28]. In these trials, a random digit number between 1 and 9 will replace the fixation cross for a duration of 150 milliseconds, and participants will be instructed to type the number on the keyboard. The intertrial interval will be 1000 milliseconds after digit trials so that participants can reposition their fingers on the keys. In the context of this study, incongruent trials will be trials where the probe appears in the opposite location previously occupied by the pain-related stimulus, whereas congruent trials will be those where the probe appears in the location previously occupied by the pain-related stimulus.

**Figure 2 figure2:**
[figure not shown]
Sample congruent trial from one of the nongamified attentional bias modification training tasks where the dot-probe replaces the top, pain-related word. Stimuli are not presented to scale.

#### Nongamified Standard ABMT

Each standard ABMT task will start with 1 block of 17 practice trials, comprising 16 neutral stimulus pairs and 1 digit trial. For each correct practice trial, the word *Correct!* will appear on the screen, whereas the word *Incorrect!* will appear for every erroneous response. The training phase will comprise 4 training blocks, each comprising 68 experimental trials (8 [12%] congruent trials; 56 [82%], incongruent trials; and 4 [6%] digit trials), totaling 272 trials and taking approximately 15 minutes to complete. The probe will replace neutral cues in 87.5% (224) of trials and pain cues in 12.5% (32) of trials, thereby training attention away from pain-related cues. This distribution will be used to reduce the obviousness of the probe contingency [29], and participants will not be made aware of it. Word pairs will be randomly presented in each of the 4 possible combinations (probe up and target down, probe down and target up, probe up and target up, and probe down and target down). The selection of a 500-millisecond presentation time for the stimulus pair is guided by previous pain ABMT studies that have shown positive training effects in individuals with chronic pain [4]. Stimuli will be presented in a randomized order across trials and participants, and trials will be intermixed and randomly presented in 4 blocks, with a rest offered between each block of trials.

#### Nongamified Sham Control ABMT

The control ABMT group will be similar to the standard ABMT group except that the probe will appear with equal frequency in the position of the pain-related and neutral words, totaling 272 trials (128 [47%] congruent trials; 128 [47%] incongruent trials; and 16 [6%] digit trials per session) and taking approximately 15 minutes to complete.

#### Gamified ABMT

The implementation of gamification has been listed within the group of complex interventions [30]. These interventions refer to activities that comprise multiple interacting components (eg, intensity and setting) that, when applied to the target population, result in a range of possible outcomes [31]. Therefore, the development of the gamified task followed the Medical Research Council framework for complex interventions [31], using theory, review evidence, and expert involvement. The gamified ABMT task was developed in several steps.

In the first step, a multidisciplinary team with research expertise in the fields of eHealth, cognitive psychology, and gamification discussed the core theories, methods, mode of delivery, implementation strategies, and design requirements. Specifically, rather than developing a completely new ABMT intervention, it was decided to design the gamified ABMT task as a so-called *game-shell* [32]; that is, game elements were added as an additional layer to the standard ABMT task without changing the initial structure. This design allows the original evidence-based ABMT paradigm to remain unchanged and has been frequently used in the gamified cognitive literature [17,32,33].

In step 2, the game elements were selected. This was guided by a qualitative and quantitative review, as well as specific theories. First, we undertook a systematic review and meta-analysis assessing the effectiveness of gamification applied to cognitive training tasks to gain a better understanding of the impact of gamification on cognitive training and identify factors that contribute to the optimal design of such programs [15]. The review identified that typically 5 game elements were used and that achievement and progression-oriented game features (eg, rewards and feedback loops) were commonly implemented in cognitive training tasks. Although the review could not show support for one feature over another (because of a limited number of studies in the subgroups), it provided evidence for the effectiveness of gamification in improving motivation and/or engagement (Hedges *g*=0.72) and synthesized findings into practical guidelines for implementing gamification for cognitive training.

Second, to increase the likelihood of the effectiveness of the intervention design and respond to the call for more theory-driven research on gamification in the field of health [15,34,35], the implementation of game elements in the ABMT procedure was guided by concepts of self-determination theory [36,37] and self-regulation [38]. According to self-determination theory [36,37], which is a well-established theoretical framework within gamification research [34], competence (ie, feeling effective), relatedness (ie, feeling connected to others), and autonomy (ie, feeling a sense of freedom) are the 3 basic psychological needs that determine intrinsic motivation, sustained engagement, and psychological well-being. Previous research has shown that these needs can be addressed by specific elements such as badges, leaderboards, performance graphs, and social competition [39-41]. Another construct that is fundamental to the success of health-related interventions is self-regulation, defined as a dynamic motivational process of setting, pursuing, and maintaining personal goals [42-44]. Self-regulation techniques such as goal setting and self-monitoring can motivate users to engage and sustain in activities, and there is evidence that these techniques can be facilitated in gamification through a range of features such as rewards, goals, levels, and progress bars [45-47].

On the basis of theoretical considerations and the empirical findings discussed in the previous sections, a combination of 5 game elements was incorporated in the gamified task to keep participants motivated and engaged in the sustained and repeated use of the ABMT procedure. The 5 gamification features are briefly described as follows:

Clear gamified goal: At the start of each training session, a clear gamified performance goal will be set for the task to earn as many points as possible and receive badges along the way. Goals that are specific and reasonably challenging are the most effective at increasing motivation and task performance [48] and are likely to increase the satisfaction of the need for competence [40].Feedback loops: During the practice phase, immediate gamified feedback will be provided to help facilitate self-monitoring [46,49] and feelings of competence [40]. For each correct practice trial, the word *Correct!* and a smiling emoticon will appear on the screen, whereas the word
*Incorrect!* and a frowning emoticon will occur in every incorrect practice trial (Figure 3).Task-related progress: During the training phase, a constantly visible progress bar at the top of the screen will indicate the proportion of trials remaining in each block, and a written indicator will reflect the number of blocks completed (Figure 3). These gamification features can facilitate self-tracking and motivate participants toward the attainment of goals [45,46] and fulfill their desire for competence [39].Rewards: Collectible points and badges were implemented to facilitate participant goal setting [45,46] and satisfy their innate psychological needs for competence, autonomy, and relatedness [40]. Specifically, between blocks of trials, participants will receive feedback about their performance in the form of points, calculated for each block of trials (1 point is earned for each correct trial; a maximum of 68 points can be earned per block). We choose to provide feedback after each block of trials rather than after each trial to ensure that the flow of training is uninterrupted. At the end of each training session, the participants will also be rewarded with a badge (Figure 3). There are 6 different badges, each of which has a number of stars on it corresponding to the number of sessions completed.Sound effect (with rewards): To enhance motivation, the task incorporates a pleasant auditory and visual reward in the form of a firework. To ensure that all participants in the gamified ABMT condition are exposed to the same type of game elements, everyone will experience the fireworks after the first block of trials. However, for subsequent blocks of trials, only those who obtain at least 60% (41/68 trials) accuracy will experience the fireworks. This latter criterion involves an element of uncertainty that can further increase motivation.

In step 3, a gamified prototype for the experimental condition was created collaboratively by the authors of this paper, who are experts in the field of gamification and cognitive psychology, and programmed using Inquisit 6.4.

In the last step, all the intervention materials and tasks (nongamified and gamified) were piloted internally by members of the research team to ensure that the program was feasible to deliver over the internet to the target sample. Following discussions, minor refinements were proposed and made to the gamified intervention. For example, the width and height of the progress bar were adjusted to make the visibility of the progression more noticeable.

